## Methods: participants, interventions, and outcomes

### Study setting {9}

The study will take place at the University of Siegen’s outpatient psychotherapeutic clinic.

### Eligibility criteria {10}

Participants must be at least 18 years old and exhibit harmful use of tobacco (F17.1 according to the ICD-10; [47]) or tobacco dependence (F17.2 according to the ICD-10) while also fulfilling the criteria for a treatment-relevant primary mental disorder. An exclusion criterion is acute suicidality, as well as the presence of an acute psychotic episode or the use of certain medications (e.g., neuroleptics such as Clozapine), where unmonitored cessation without a psychiatrist’s oversight may pose significant risks. The smoking intervention will be performed by trained clinical psychologists, while all psychotherapeutic consultations will be performed by trained psychological psychotherapists. If additional substance use disorders are present, treatment of these disorders is prioritized in accordance with German clinical guidelines [62] and ethical standards, particularly when inpatient treatment is indicated. Smoking cessation is then offered as an adjunctive treatment once the primary substance-related condition is overcome. This approach ensures appropriate care and participant safety.

### Who will take informed consent? {26a}

The informed consent of study participants is ensured through a comprehensive briefing at the initiation of the study (initial session) by the clinical psychologist. After receiving and reviewing the information, participants’ consent will be obtained.

### Additional consent provisions for collection and use of participant data and biological specimens {26b}

Not applicable.

## Interventions

### Explanation for the choice of comparators {6b}

By comparing the intensified smoking cessation program implemented prior to psychotherapy to a waiting control condition, we aim to evaluate the effectiveness and potential superiority of our approach regarding smoking cessation success and improvement in mental health symptoms. It is important to acknowledge that participants in both conditions may seek or receive other forms of psychotherapeutic treatment during the post- and 6-month follow-up assessments. To account for this, we will inquire about any additional treatments participants may have undergone and control for these variables in our analysis. Specifically, all additional treatments will be systematically documented and coded as categorical variables (e.g., concurrent individual psychotherapy, group therapy, psychopharmacological treatment). Dummy variables representing the presence or absence of each treatment type will be included as covariates in the repeated-measures ANOVAs. This approach not only ensures a more accurate comparison but also reflects the naturalistic conditions under which the study is conducted.

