### Objectives {7}

We expect a treatment effect of the intensified smoking cessation on variables regarding tobacco dependence severity, smoking behavior as well as mental health outcomes, as evidenced by a reduced nicotine dependence severity, reduced smoking intensity, a higher quality of life and subjective psychological well-being, and reduced perceived impairment of mental health symptoms and depressive symptoms in patients in the experimental condition receiving a smoking cessation intervention than in patients in the wait-list-control condition. These changes are expected to become apparent both in the short-term (i.e., post-treatment) as well as the long-term (i.e., 6 weeks and 6 months follow-up) when compared to the baseline measures.

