### Trial design {8}

The present research project demonstrates a single-center randomized controlled trial examining the impact of an intensive smoking cessation treatment compared to a waiting control condition on tobacco dependence and mental health symptoms related to the primary mental disorder among smokers aiming to initiate outpatient psychotherapy. All participants included in the study are receiving three psychotherapeutic consultations and fulfill an indication for psychotherapy. We chose to include a waiting control condition instead of an active (unspecific) control condition for comparison as a waiting control condition mirrors the typical course for patients awaiting psychotherapy, making the findings more applicable to real-world clinical settings. Eligible participants will be randomly assigned to either the experimental condition (immediate diagnostic session, a six-session smoking cessation program and a self-guided digital health application) or the waiting control condition (diagnostic sessions only). Patients randomly assigned to the control condition will be placed on a wait-list and will receive the smoking cessation intervention after 6 months. Post-treatment assessments for the intervention group will occur three weeks after their initial diagnostic session, which marks the end of the treatment phase. Similarly, participants in the control condition will undergo post assessments 3 weeks after their initial diagnostic session. Follow-up assessments for both groups will take place at 6 weeks (follow-up 1) and 6 months (follow-up 2) after the completion of the post-treatment assessments.

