### Relevant concomitant care permitted or prohibited during the trial {11d}

There is no specific concomitant care administered nor prohibited during the trial.

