### Participant timeline {13}

Smoking patients who have had three psychotherapeutic consultations at the Psychotherapeutic Outpatient Center of the University of Siegen will be informed about the option of participation in the current study. Interested participants will be contacted by the study team and undergo a telephone interview to determine eligibility and fulfillment of the inclusion criteria (*− t*_1_). Following telephone screening for a duration of 10–30 min, patients will be invited to the first smoking cessation session, during which informed consent will be obtained and psychological symptoms will be assessed within the course of a diagnostic session (baseline, *t*_*0*_). After the diagnostic session, during which all baseline measures will be assessed, patients will be randomly assigned either to the experimental group or the passive control group. The experimental condition will receive a 6-step smoking cessation program and additional access to a smartphone-based self-help application. The duration of the intervention will be three weeks. Afterwards, patients will be invited again to assess all measures of interest (*t*_1_). Six weeks (*t*_2_) and 6 months (*t*_3_) after completion, patients will be invited once again for follow-up assessments. The participants’ timelines and data assessment points are shown in Table 2..

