### Sample size {14}

To estimate the required sample size, an a priori power analysis was conducted using G*Power 3.1.9.7 [21]. The primary hypothesis will be tested using a 2 × 4 mixed-design repeated-measures ANOVA (with a power of 1 − *β* = 0.80 and a significance level of *α* = 0.05. This requires a sample size of approximately 62 participants in total, 31 per condition, to detect a moderate effect. No additional participants will be recruited to compensate for potential dropout; instead, the study design follows the intention-to-treat (ITT) principle and employs multiple imputation methods to address missing data. The decision to target a moderate effect size is driven by practical considerations to detect treatment effects that are both statistically significant and practically meaningful.

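### The primary repeated-measures ANOVAs are to adjust for treatment taken up after randomisation, so the adjusted contrast is no longer the effect of allocation that the ITT rationale is meant to protect

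*Protocol article*

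**What the plan says.** The protocol article, Explanation for the choice of comparators {6b}, expects that "participants in both conditions may seek or receive other forms of psychotherapeutic treatment during the post- and 6-month follow-up assessments". It has these treatments documented and coded by type (individual psychotherapy, group therapy and psychopharmacological treatment are its examples). It then fixes the analysis: "Dummy variables representing the presence or absence of each treatment type will be included as covariates in the repeated-measures ANOVAs". The reason given is: "This approach not only ensures a more accurate comparison but also reflects the naturalistic conditions under which the study is conducted".

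Other sections set the context:

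- Participant timeline {13}: after the baseline session (t0), "patients will be randomly assigned either to the experimental group or the passive control group".
- Trial design {8}: "All participants included in the study are receiving three psychotherapeutic consultations and fulfill an indication for psychotherapy".
- Relevant concomitant care {11d}: "There is no specific concomitant care administered nor prohibited during the trial".
- Statistical methods {20a}: each continuous primary outcome is tested by a mixed 2 (condition) × 4 (time) repeated-measures ANOVA. That section lists no covariates.
- Sample size {14}: "the study design follows the intention-to-treat (ITT) principle". The missing-data section {20c} justifies ITT as a protection against bias in the treatment effect.
- Objectives {7}: "These changes are expected to become apparent both in the short-term (i.e., post-treatment) as well as the long-term", the long term being the 6-week (t2) and 6-month (t3) follow-ups.

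**The concern.** The only ANOVAs over time that the protocol names are the primary tests, so the dummies belong to the primary model. Treatment begun after t0 can respond both to allocation and to how a patient's symptoms develop. Holding it fixed gives up the comparison that randomisation protects.

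The result is not a therapy-free effect either. Patients who seek therapy because they are doing badly differ from those who do not, and the dummy absorbs that difference together with any effect of the therapy. If uptake differs between arms, the adjustment can produce a group difference where none exists or remove part of a real one. The second case is awkward for this trial: if the programme works and worse patients seek therapy, uptake diverges because of the benefit, and the adjustment takes some of the benefit away.

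**Working it through.** **Plan's own figure.** Sample size {14} gives 62 patients (31 per arm), α = 0.05, power 0.80 and a moderate effect. With f = 0.25 (assumed; the article gives no number), m = 4 visits and noncentrality λ = f²(N − 2)(m − 1) = 0.0625 × 60 × 3 = 11.25 on 3 and 180 df, power is 0.804. The figure reproduces. It assumes no covariates, so it is unchanged by the fix below.

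**How the dummy can enter.** {6b} does not say.

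1. *One value per person, between-subject main effect only.* A term constant over time drops out of every within-person difference. The group main effect changes; the group × time test does not.
2. *One value per person, crossed with time*, as in the usual repeated-measures ANCOVA. The group × time test changes.
3. *One value per visit.* The group × time test changes, but little.

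**Size in case 2.** Adjusted contrast = unadjusted contrast − γ × Δ, where Δ is the uptake difference between arms and γ the within-arm difference in change between takers and non-takers. If Δ = 0 the shift is nil.

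All simulation inputs are assumptions: 31 per arm, SD 1, correlation 0.6 with t0 and 0.75 among t1 to t3, one dummy, Greenhouse-Geisser group × time test at 0.05 before Benjamini-Hochberg, 6,000 trials per case. Uptake logit = a + slope × (mean of t1 and t2 minus t0) + arm term, so patients who worsen are likelier to start treatment. Simulated γ is 0.27, 0.48 and 0.64 SD at slopes 0.5, 1.0 and 1.5. The t3 shift is then:

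- 20-point gap: 0.27 × 0.20 = 0.05, 0.48 × 0.20 = 0.10, 0.64 × 0.20 = 0.13 SD.
- 40-point gap: 0.27 × 0.40 = 0.11, 0.48 × 0.40 = 0.19 (simulated 0.20), 0.64 × 0.40 = 0.26 SD.

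Rejection with no programme effect (without the dummy: 4.1% to 5.3%):

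| Uptake, % by arm | Slope 0.5 | Slope 1.0 | Slope 1.5 |
|---|---|---|---|
| equal | 4.1% | 5.2% | 5.6% |
| 55 v 45 | 5.4% | 6.2% | 6.1% |
| 60 v 40 | 6.0% | 7.2% | 10.1% |
| 70 v 30 | 7.8% | 15.4% | 26.3% |

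Reversing the arms gives similar values (5.9%, 7.8%, 9.6% at 20 points; 7.5%, 16.2%, 25.4% at 40).

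True benefit 0.5 SD, no direct arm effect on uptake (power without the dummy 62.9%, t3 estimate 0.50):

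| Slope | Resulting uptake, % | Power with dummy | t3 estimate |
|---|---|---|---|
| 0 | 50 v 50 | 61.8% | 0.501 |
| 0.5 | 47 v 53 | 59.7% | 0.485 |
| 1.0 | 44 v 55 | 54.5% | 0.449 |
| 1.5 | 43 v 57 | 47.2% | 0.410 |

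The identity agrees: at slope 1.5, 0.50 − 0.64 × 0.14 = 0.41.

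**Size in case 3.** Dummy 0 at t0 and t1, half of takers started by t2, all by t3. Null rejection at 20- and 40-point gaps is 4.4% to 5.1%, with a t3 shift of 0.01 to 0.07 SD. With a 0.5 SD benefit, power goes from 62.0% to 61.6%, 61.0% or 60.4% at the three slopes.

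**Does case 2 recover a therapy-free effect?** Let psychotherapy be worth 0.5 SD at t3, the programme nothing, and uptake 60% v 40%. The ITT effect is 0.5 × (0.60 − 0.40) = 0.10 SD; the therapy-free effect is 0. The adjusted estimate is 0.00 at slope 0, 0.05 at slope 0.5 and 0.13 at slope 1.5. It hits the target only when uptake is unrelated to course.

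**Second simulation with a different set-up** (4,000 trials, sphericity assumed, dummy crossed with time; negative = improvement; direct effect −0.5, add-on effect −0.5 in the first three):

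- Uptake 30% programme v 60% control, no selection: true ITT −0.5 − 0.5 × (0.30 − 0.60) = −0.35; unadjusted −0.350, adjusted −0.498.
- Rates reversed: true ITT −0.65; unadjusted −0.649, adjusted −0.502; power 0.576 to 0.406.
- 30% v 60% with uptake also driven by poor course: −0.355 unadjusted, −0.360 adjusted. Two distortions cancelled, so direction cannot be predicted.
- No effects at all, uptake driven by poor course: rejection 0.072 at 30% v 60%, and 0.160 at 20% v 70% with stronger selection, against about 0.05 unadjusted.

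**The case against.** The strongest reply is that the plan leaves the form of the dummy open, and of three forms one leaves the group × time test untouched and another barely moves it. Such detail is commonly left to a SAP, which is not shown. A reader might infer from {6b} that the primary interaction test is necessarily distorted; the documents do not support that. What the article does fix, without condition, is that these covariates go into the primary model, and no section calls this a sensitivity analysis. The absence of covariates from {20a} does not withdraw it.

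A reader might also infer that ITT has been abandoned. It has not: everyone randomised is analysed as allocated, and ITT is invoked mainly for dropout and missing data. No estimand is defined. What changes is the quantity estimated, and with it the protection from bias that {20c} gives as the reason for ITT.

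The 26% figure needs a 40-point gap and strong selection. Nothing in the documents points to such a gap. Both arms come from one clinic under one concomitant-care rule, so equal uptake, and no shift, is possible. The rates are also for single tests, before Benjamini-Hochberg control.

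Finally, the selection argument needs the analysed outcome to drive uptake. That is plausible for WHO-5, WHOQOL-BREF, BSCL and BDI-II. It is not shown for the Fagerström score, ASSIST tobacco or exhaled CO, so the figures should not be read across to those three.

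**Conclusion.** The point stands in a limited form. The stated rule conditions the primary tests on variables that arise after randomisation. The adjusted contrast is then neither the effect of allocation nor, unless uptake is unrelated to symptom course, a therapy-free effect. The claim of greater accuracy in {6b} is unsupported.

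The harm runs from nil (equal uptake, or a main-effect-only dummy as far as the interaction is concerned), through small (per-visit dummy), to material (person-level dummy crossed with time and a clear uptake gap). It bears mainly on the mental-health outcomes at t2 and t3, since little uptake can occur in the three weeks before t1. Uptake rates, the link between symptoms and uptake, and the correlations are all assumptions. The plan should be changed because the conflict is plain and the remedy cheap; confidence that it would alter this trial's results is only moderate.

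**What to change.** In {6b} and {20a}, state that the primary ANOVAs carry no covariate for treatment begun after randomisation. Treatment already running at t0 may stay as a baseline covariate. Move the dummy-adjusted model to Methods for additional analyses {20b}, which already allows re-evaluation for confounding, label it a sensitivity analysis, and say there whether each dummy has one value per person or per visit and whether it is crossed with time. Report additional-treatment uptake by arm beside the mental-health results. Word the t2 and t3 conclusions as the effect of offering the programme with other treatment permitted in both arms. Delete the accuracy claim.

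The cost is close to nothing. The treatments are already to be documented, no new data are needed and the sample size is unaffected. Data collection runs to April 2027 (Trial status), so the change can be made before outcomes are analysed. The one downside is that the primary contrast will include any difference in later treatment that the programme itself causes, so it does not isolate a direct effect.

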### Intervention description {11a}

The intervention for the experimental group consists of a manual-based six-step smoking cessation program, adapted from the widely implemented and continuously evaluated smoking cessation program developed by the *Arbeitskreis Tabakentwöhnung* (Smoking Cessation Working Group) at the University Hospital for Psychiatry and Psychotherapy in Tübingen. This program, detailed in the manual by Batra and Buchkremer [3] and recently updated [4], is rooted in cognitive–behavioral therapy (CBT) and designed for both group and individual settings, though this study will utilize the individual setting. The program spans six sessions, during which participants will receive guidance on preparing for and executing their smoking cessation efforts, developing strategies to maintain abstinence, and preventing relapse. The sessions are organized into three distinct phases, as outlined in Table 1.

**Table 1 Tab1:** Smoking intervention phases in the intervention group

Phase 1	Session 1	Abstinence preparation phase: Focuses on motivating individuals and understanding their smoking habits
	Session 2	
Phase 2	Session 3	Cessation phase: Provides specific strategies for quitting smoking and managing cravings
	Session 4	
Phase 3	Session 5	Stabilization phase: Emphasizes building alternative behaviors, coping with potential relapse triggers, promoting overall health, and managing relapses
	Session 6	

Additionally, personalized recommendations tailored to each individual’s smoking behavior will be provided. Detailed descriptions of the individual sessions are outlined in the manual by Batra and Buchkremer [4]. In this research project, we will augment the original program by increasing session frequency and incorporating a self-help smoking cessation smartphone application to address specific challenges faced by smokers with mental disorders. While the original program was designed with weekly sessions over a course of 6 weeks, our intensified version will include two sessions per week, shortening the intervention duration to three weeks. Furthermore, participants will have access to the digital health application (*NichtraucherHelden®*,Sanero Medical GmbH, Stuttgart, Germany), a CBT-based self-help app featuring eight modules of psychoeducation, tasks, and relapse prevention. Recent evidence from a nationwide, multicentric, parallel, randomized controlled trial demonstrated the app’s feasibility and efficacy, with the intervention condition showing twice the abstinence rates at a 7-day point prevalence compared to the control condition [54].

### Criteria for discontinuing or modifying allocated interventions {11b}

The assigned intervention can be terminated upon the patient's request, and participants may withdraw from the study for any reason. Researchers retain the authority to discontinue a patient's participation in the study if their mental health condition worsens, such as through experiencing a psychotic episode, exhibiting an acute increase in suicide risk, or an indication for hospitalization.

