#### Primary outcomes targeting mental health symptoms

Changes in mental health symptoms related to mental disorders are measured by self-report questionnaires, which will also be assessed at the four measurement points mentioned above (baseline, post, follow-up 1 and 2). The questionnaires target general psychological well-being and perceived quality of life, symptoms associated with mental disorders, and depressive symptoms.

Changes in mental health status over time are operationalized as follows:Mean score changes in the German version of the “WHO-5 Well-being Index” ([WHO-5]; [52]).Mean score changes in the German version of the “WHO Quality of Life-BREF” ([WHOQOL-BREF]; [1]).Mean score changes in the “Brief Symptom Check List” ([BSCL]; [23])Mean score changes in the “Beck Depression Inventory-Revised” ([BDI-ll]; [6]).

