## Assignment of interventions: allocation

### Sequence generation {16a}

Participants will undergo random allocation to either the experimental or control condition at a 1:1 ratio. Given the study design, participant or therapist blinding post-allocation is not feasible.

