### Methods in analysis to handle protocol non-adherence and any statistical methods to handle missing data {20c}

Multiple imputation will be used to address missing data for intention-to-treat (ITT) analyses, as ITT prevents biases in the treatment effect [27]. Specifically, multiple imputation by chained equations will be applied under the assumption that data are missing at random. The imputation model will include baseline scores, group assignment, and other relevant predictors of missingness. In addition to the ITT analyses, exploratory per-protocol analyses may be conducted to gain further insight into the effects among participants who completed the study as intended.

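### Worsening mental health can end study participation as well as treatment, so primary-outcome values may be lost because of their level

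*Protocol article*

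**What the plan says.** Section {11b} of the protocol article deals with discontinuing or modifying the allocated intervention. Its first sentence treats two things separately: the patient may ask for the intervention to end, and the patient may leave the study. The second sentence gives staff the wider of these powers: they may end a patient's "participation in the study if their mental health condition worsens, such as through experiencing a psychotic episode". The further examples are "exhibiting an acute increase in suicide risk, or an indication for hospitalization". They are introduced as examples, so the list is open.

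The outcomes section makes mental health a primary domain, covering well-being and quality of life, "symptoms associated with mental disorders, and depressive symptoms". Its four instruments are the WHO-5, WHOQOL-BREF, BSCL and BDI-II. They are measured at baseline, at t1 (3 weeks later), and at t2 and t3 (6 weeks and 6 months after t1).

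Section {20c} uses multiple imputation by chained equations under missing at random: "The imputation model will include baseline scores, group assignment, and other relevant predictors of missingness". The other predictors are not named. Section {14} plans 31 patients per condition and adds: "No additional participants will be recruited to compensate for potential dropout". Section {16a} states that "participant or therapist blinding post-allocation is not feasible". Section {18b} on retention offers information and reminder calls, and says nothing about patients whom staff have removed.

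**The concern.** The trigger for removal is close to what four primary measures record. A patient who deteriorates can be taken out of the study by staff decision, and the later scores that would have shown the deterioration are then not collected. Missing at random holds for such values only if the imputation model contains what drove the removal. Baseline score and arm do not contain a deterioration that happens after baseline. The imputed values would then tend to be too good, and the mean of the affected arm would look too favourable at visits after removal.

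Whether this reaches the treatment contrast depends on whether the two arms lose patients differently. They could, for two reasons. The decision is discretionary and taken by people who know the allocation. The experimental arm also has six extra contacts at which worsening can be noticed, although these are confined to the start: "our intensified version will include two sessions per week, shortening the intervention duration to three weeks". After t1 the planned visits are the same in both arms.

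This is a rule of conduct, not an omitted analysis detail. A later analysis plan can model missing values but cannot recover values that nobody collected.

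**Working it through.** **The plan's own figure.** The article states 62 patients, 31 per condition. With a moderate effect read as f = 0.25 (the article gives no number), alpha 0.05, two groups, four measurements and sphericity, the noncentral F test of condition by time, with noncentrality f² × (N − 2) × 3, first reaches 80% power at N = 62 (power 0.804). The figure is reproducible and not in dispute. It matters here because one removal is 1/31 = 3.2% of an arm.

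**Simple formula.** Let p be the proportion of an arm removed, and s the number of SDs by which removed patients are truly worse than the values imputed for them. The arm mean is too favourable by p × s, so

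bias of the contrast in favour of the intervention = pE × sE − pC × sC.

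The document gives neither p nor s. With s = 1.5 assumed in both arms:

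| Removed, experimental v control | Calculation | Bias (SD) |
|---|---|---|
| 1 v 1 | (1 − 1)/31 × 1.5 | 0 |
| 2 v 1 | (2 − 1)/31 × 1.5 | 0.048, for the intervention |
| 3 v 1 | (3 − 1)/31 × 1.5 | 0.097, for the intervention |
| 1 v 3 | (1 − 3)/31 × 1.5 | 0.097, against it |

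For 3 v 1, s = 1.0 gives 0.065 and s = 2.0 gives 0.129.

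**Simulation.** There were 2 million patients per arm. Baseline and outcome have SD 1 and correlation rho, and higher is worse. Patients whose change exceeds a threshold are removed with probability q, and their values are imputed by within-arm regression on baseline. The bias is in experimental minus control, so a negative value favours the intervention.

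| q, experimental / control | True effect (SD) | rho 0.5, threshold 1.0 SD | rho 0.7, threshold 1.5 SD |
|---|---|---|---|
| 0.50 / 0.50 | 0 | 0.00 | 0.00 |
| 0.75 / 0.25 | 0 | −0.118 | −0.021 |
| 0.25 / 0.75 | 0 | +0.117 | +0.021 |
| 0.50 / 0.50 | −0.5 | +0.050 | +0.016 |

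In the first row at rho 0.5, each arm loses 7.9% of its patients and its mean is 0.102 SD too favourable, but the errors cancel. In the second row, 11.9% v 3.9% are removed. The last row shows that an equal rule can still bias the contrast: when the intervention works, fewer of its patients cross the threshold, so more poor values are lost from the control arm.

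**A second removal model.** Here the patients who worsen most are removed in fixed percentages (control/intervention), with rho 0.5 and the same imputation. The biases are about −0.08 SD at 0/5, −0.16 at 0/10, −0.07 at 5/10, −0.14 at 5/15, 0 at 10/10 and +0.07 at 10/5. The pattern is the same: bias appears when removal differs by arm and largely cancels when it does not.

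**The case against.** The strongest reply is that this is a permissive safety rule with severe examples. Removal is not mandatory, and acute suicidality and acute psychosis already exclude patients at entry, so events may be few. Many such patients could not validly complete self-report questionnaires at the time, whatever the rule said.

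The lenient simulation also goes beyond the named triggers. At rho 0.5 the change has SD √(2 × 0.5) = 1, so about 16% of patients cross a 1 SD threshold. That is ordinary worsening. In the strict case the change has SD √(2 × 0.3) = 0.77, about 2.6% cross 1.5 SD, and the bias is at most 0.02 SD. The standard error of an unadjusted contrast is about √(2/31) = 0.25 SD, so the 2 v 1 case is about a fifth of it.

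The planned imputation may also do better than regression on baseline alone, since worsening already recorded at t1 or t2 could inform later values. Finally, an article condenses a fuller protocol, and the intention-to-treat commitment keeps removed patients in the analysis.

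Most of this stands as a limit on size. It does not remove the point. The article states a rule, in words that distinguish the study from the intervention, and attaches the wider power to worsening mental health. The open list allows removal for less than the named events. Intention-to-treat keeps the patient in the denominator but does not supply the missing score. Safety justifies stopping treatment; it does not by itself require ending assessment of a patient who consents and can be assessed.

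**Conclusion.** The concern holds as a weakness of design that is cheap to correct. As worded, the rule can lose primary mental health values because of their level, and the stated imputation need not make up for that. The effect on the contrast may be near zero, may favour the intervention or may work against it; the document does not settle which. On assumed inputs it ran from zero to about 0.12 SD in either direction under the lenient trigger, up to about 0.16 SD in the second removal model when only the intervention arm lost patients (10%), and at most 0.02 SD under the strict trigger. These figures rest on assumed removal rates, correlations and severity, and on imputation from baseline within arm. They illustrate the mechanism and do not forecast its size.

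**What to change.** Keep the clinical criteria in section {11b}, and state that meeting them stops the intervention only (in the control arm, the later offer of it). The t1 to t3 assessments then continue in both arms unless the patient withdraws consent to data collection or cannot be assessed, and the event and its date are recorded. Optionally, section {20c} can name the recorded event among the predictors of missingness. A sensitivity analysis that shifts values still missing after the event towards worse scores can be left to the SAP.

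The cost is one or two sentences. The visits are already planned and the sample size does not change. The limitation is that some patients who are acutely psychotic or in hospital will still not be assessable, so only part of the data is recovered.
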